### Sample size justification

Two different calculations were made to justify the sample size for this study. First, a precision-based calculation for the ICC of Vc was based on previous reliability studies [27, 28]. For this calculation, we used RStudio, Version 1.3.959 and the "Nest"-function from the "ICC" package version 2.3.0 [40]. Assuming the lowest ICC reported of 0.92 [28], two measurements per subject and an alpha level of 0.05, we will need 18 subjects to achieve the desired precision with a confidence interval of 0.15.

Second, to estimate how many subjects we will need to detect an effect of changing the interstimulus-interval on Vc, we used the raw data provided by Wilson et al. [31]. From those data, we calculated Vc_10-90%_ = 0.8 Dm / Tc and Vc_norm_ = 0.8 / Tc (S1 Table). As only Dm and Tc were included in those raw data, we could not apply the other three formulas. We performed a two-way (ISI x measure) repeated measures analysis of variance (ANOVA) to estimate the main effect of inter-stimulus interval on Vc_10-90%_ and Vc_norm_. We obtained effect sizes using RStudio and the "eta2_to_f"-function from the "effectsize" package [41] and calculated the sample size using the "wp.rmanova"-function from the "WebPower"-package [42]. For the sample size calculation, we assumed three groups, ten measurements per subject, an effect size f = 3.1 (Vc_10-90%_) and f = 1.6 (Vc_norm_), a nonsphericity correction coefficient of 0.7 (Vc_10-90%_) and 0.6 (Vc_norm_), an alpha level of 0.01, a power of 0.95 and a between effect, a total of 9 (Vc_10-90%_) subjects and 18 (Vc_norm_) subjects were needed. We confirmed the estimated sample size for the ANOVA by repeating the calculations for both Vc_10-90%_ and Vc_norm_ using g*power v3.1.9.2 [43]. Based on the results of both calculations for the ICC and the ANOVA and accounting for potential dropouts, we intend to recruit 24 subjects.

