To assess the effects of different ISI on Vc during repeated stimulation, we will employ a within-subject repeated-measures ANOVA. The two independent variables will be ISI (10 s, 20 s, 30 s) and stimulus number (stimulus 1 to stimulus 10). The dependent variables will be Vc_0-10%_, Vc_0-90%_, Vc_10-90%_, Vc_norm_ and Vc_Dm/t90%_ for both the RF and BF, respectively. Pairwise comparisons with Bonferroni correction will applied for significant main effects. The effect size Cohen’s d will be calculated as d = M_diff_ / √SD_1_ + SD_2_ / 2 [53] for pairwise comparisons to allow comparisons between effects of different ISI and between consecutive stimuli. Thresholds for small, moderate, large, very large or extremely large effects will be 0.2, 0.6, 1.2, 2.0 and 4.0 [54].

Statistical significance will be set at alpha ≤ 0.05. Missing data will be handled by listwise deletion of cases with missing data [55]. All statistical analyses will be performed using R studio and respective packages. Upon completion of the data collection and analysis, the raw data disaggregated by sex and the analysis code will be openly available at https://osf.io/4du2j/?view_only=ee7a4afb30514cb9a2e15381282dcec8.

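### The inter-stimulus-interval (ISI) ANOVA is sized at alpha 0.01 but tested at 0.05, with no error control across its eight distinct formula-by-muscle tests

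*Protocol article*

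**What the plan says.** Two sections of the protocol article fix a significance level for the same analysis.

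- **Sample size justification.** The number of subjects needed to detect an ISI effect is calculated with "an alpha level of 0.01, a power of 0.95 and a between effect". The result is that "a total of 9 (Vc_10-90%_) subjects and 18 (Vc_norm_) subjects were needed". With the separate ICC calculation and an allowance for dropout, the plan is: "accounting for potential dropouts, we intend to recruit 24 subjects". No reason is given for 0.01.
- **Statistical analysis.** "Statistical significance will be set at alpha ≤ 0.05". This stands for all analyses. For the ISI ANOVA, "The dependent variables will be Vc_0-10%_, Vc_0-90%_, Vc_10-90%_, Vc_norm_ and Vc_Dm/t90%_ for both the RF and BF, respectively", which makes 5 × 2 = 10 ANOVAs. Bonferroni is attached only to the pairwise comparisons that follow a significant main effect. No rule is stated across the ten ANOVAs.

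Two other places matter. The Introduction states one hypothesis, that Vc changes with ISI, and names no leading formula or muscle. The section on calculation formulas defines Vc_0-90% as 0.9 × Dm / (Td + Tc) and Vc_Dm/t90% as Dm / (Td + Tc).

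**The concern.** The two levels contradict each other, and both are fixed in the article rather than left to a later plan. The planning level is the stricter one, so the effect of following the analysis section is on false positives, not on power.

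Because the hypothesis names no formula or muscle, a significant ISI effect in any one of the ANOVAs could be presented as support for it. The Bonferroni step does not help, since it starts only after an omnibus test has already passed at 0.05. The results are meant to inform a standardized measurement approach, so a chance finding for one formula in one muscle could influence the choice of rest interval. The protocol is also to be preregistered before recruitment. With two levels on record, the decision rule could still be chosen after the data are seen.

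**Working it through.** **1. Reproduce the plan's sample size.** Inputs from the Sample size justification: 3 groups, f = 3.1 (Vc_10-90%) and 1.6 (Vc_norm), nonsphericity coefficients 0.7 and 0.6, alpha 0.01, power 0.95, between effect. Noncentral F with df1 = 3 − 1 = 2, df2 = n − 3 and λ = f² × n × coefficient.

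- Vc_10-90%: λ = 9.61 × 0.7 × n = 6.727n. Power 0.95 is reached at n = 8.5, so 9 (stated: 9).
- Vc_norm: λ = 2.56 × 0.6 × n = 1.536n. Power 0.95 is reached at n = 18.5, so 19 (stated: 18, where power is 94.0%).

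The stated figures are reproduced to within one subject, so 0.01 was the level actually used.

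**2. Effect of the level on sample size, same formula.**

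| Alpha | n for Vc_10-90% | n for Vc_norm |
|---|---|---|
| 0.05 | 7 | 14 |
| 0.01 | 9 | 19 |
| 0.05/8 = 0.00625 | 10 | 20 |
| 0.05/10 = 0.005 | 10 | 21 |

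All are below 24. Power for Vc_norm at n = 24 is 99.95% at 0.05, 99.4% at 0.01 and 98.5% at 0.005.

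**3. Count the distinct tests.** Vc_0-90% = 0.9 × Vc_Dm/t90%. Multiplying an outcome by a constant leaves its F statistic and p-value unchanged. In every simulated run below, the two formulas gave the same decision. That leaves 4 distinct formulas × 2 muscles = 8 distinct ISI tests.

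**4. Bounds on the chance of at least one false ISI effect.** Only the ISI main effect is counted.

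- Eight independent tests at 0.05: 1 − 0.95⁸ = 33.7%. At 0.01: 1 − 0.99⁸ = 7.7%.
- Formulas so highly correlated that each muscle carries one effective test, muscles independent, at 0.05: 1 − 0.95² = 9.75%. This falls further if the muscles are correlated as well.

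**5. Simulation with the actual formulas.** The remaining formulas share Dm, Td and Tc, so the truth lies between these bounds. Dm, Td and Tc were simulated in two muscles for 24 subjects and three ISIs with no true ISI effect, the formulas were computed, and each ISI effect was tested by a repeated-measures F test (10,000 runs per scenario). The assumptions, none of which the article gives, were:

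- within-subject log-SDs of 2% to 10%;
- correlation 0 or 0.5 between Dm and each time parameter;
- between-muscle correlation 0 or 0.8.

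At 0.05 per test, the chance of at least one false ISI effect ranged from 16.3% to 26.1%. Simulations of the same kind at 0.01 per test gave about 4% to 7%.

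**The case against.** The strongest case on the other side has four parts.

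- **Planning at a stricter level than the test is conservative.** This stands. A reader might infer from the mismatch that the study is too small, but testing at 0.05 needs fewer subjects than were planned for. The value 0.01 equals 0.05/5 and may have been meant as a correction for five formulas, but the article does not say so.
- **The error rate is easily overstated.** A reader might take ten tests at 0.05 and arrive at 1 − 0.95¹⁰ = 40.1%. The article's own formulas rule this out, because two of the five give the same test and the others share their components. Any narrower range depends on assumed correlations.
- **No section says that one significant test confirms the hypothesis.** This is true. The study can be read as a parallel, formula-by-formula methods comparison with effect sizes and open data, and family-wise control across parallel formulas is partly a matter of judgement. It does not remove the point: one hypothesis is stated without a leading formula or muscle, and the planned level and the test level still disagree.
- **Sphericity.** A reader might also infer that the F tests will be run uncorrected, because the sample size assumes coefficients of 0.7 and 0.6 and the analysis section names no correction. The article does not say that. Silence on this detail in a condensed article is no error, and the planning coefficients show that the authors had the issue in mind.

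**Conclusion.** The point holds. The planning level (0.01) and the testing level (0.05) are unreconciled, and nothing controls error across the omnibus ISI tests. As written, the chance of at least one false ISI effect is roughly 10% to 34%. About 16% to 26% is the plausible part of that range under the simulated correlations. The upper end requires eight independent tests. The lower end requires near-perfect correlation among formulas with independent muscles, and correlated muscles would take it lower still. At the planned 0.01, the chance would be about 4% to 7% in simulation and at most 7.7% if the eight tests were independent.

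The sample size is adequate at either level. That statement takes the plan's effect sizes and its between-effect model as given; whether that model suits a single-group within-subject design is a separate question.

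**What to change.** Reconcile the Sample size justification with the Statistical analysis section before preregistration, in one of two ways.

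- Apply Holm at a family-wise 0.05 across the eight distinct omnibus ISI tests, counting Vc_0-90% and Vc_Dm/t90% as one test per muscle.
- Or carry the planned alpha of 0.01 into the omnibus ISI tests, and state that this controls the family-wise error only approximately.

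The Bonferroni step for pairwise comparisons can stay as it is, and 0.05 can stay for the M1-M2 and M1-M3 bias t-tests.

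The cost is a sentence or two and somewhat stricter ISI tests. Holm's strictest step, 0.05/8 = 0.00625, needs 10 and 20 subjects on the plan's own inputs, against 24 to be recruited. Power for Vc_norm at n = 24 stays at about 98% to 99%.

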**Fig 1 pone.0262156.g001:**
[figure not shown]
Schematic illustration of the study flow. M1, M2, M3: Measurement time points 1,2,3, respectively, mA: Milliampere, ISI: Inter-stimuli interval.

A single rater with more than three years of experience performing TMG measurements will perform all tensiomyographic measurements across two consecutive days. The individual maximum radial displacement curve of both the RF and BF will be determined two times on the first day (M1, M2), separated by a three-minute pause, and a third time on the second day (M3), 24 h after the first measurement. On the second day and three minutes after the third measurement, we will apply three blocks of ten consecutive stimuli each. The rest intervals between consecutive stimuli in each block will be 10 s, 20 s and 30 s, respectively. The rest period between block 1, block 2 and block 3 will be three minutes, respectively. We will randomize the order of the three blocks with the different ISI for each participant.

On the first day, we will familiarize all participants with the electrical stimulation procedure by applying two stimuli with a duration of 1 ms each at 20 mA and 30 mA to the RF, followed by a three-minute rest before starting the actual measurement [31]. All measurements will be taken at the same time of the day, and a constant room temperature of 21° C. Participants will be asked to refrain from caffeine intake for 2 h preceding all measurements [37] and to avoid alcohol consumption and fatiguing exercise for 24 h before the start and during the trial to counteract possible confounding. Further, participants will be asked to record their total dietary intake during the 24 h before the first appointment and replicate their intake during the 24 h before the second visit [26] (S1 Appendix).

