### Randomization and blinding

We will use an online program [38] and a block randomization procedure with four blocks of six unique numbers [39] to determine the order of ISI during repeated stimulations for each participant. To blind the rater from previous measurements, we will choose the settings of the TMG measurement software as not to display prior measurements.

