The electrical stimulation will consist of single, monophasic, square wave stimuli with a duration of 1 ms each to elicit single isometric twitches. The stimulation will start at an initial stimulation amplitude of 30 mA, and will be then increased in steps of 10 mA. During M1, M2 and M3, we will apply progressive electrical stimuli with rest-intervals of 15 s between consecutive stimuli to obtain the individual maximal displacement. The stimulation amplitude will be increased until there is no further increase of the maximum radial displacement or until the stimulator’s maximum output (110 mA) is reached. During the three blocks of repeated stimulation at 50 mA on the second day, the rest intervals between consecutive stimuli will be 10 s, 20 s and 30 s, respectively.

From M1, M2 and M3, the two displacement curves with the highest radial displacement of each measurement will be averaged respectively and used for further analysis. From block 1, block 2 and block 3, we will use every single displacement curve for further analysis.

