Further, information on the optimal rest interval between consecutive stimuli during progressive electrical stimulation is lacking. Again, only two studies have investigated the effect of different ISI on tensiomyographic parameters [31, 32]. One study investigated the effect of different ISI (30 s, 10 s, 5 s) on Dm and Tc of the rectus femoris muscle during ten consecutive stimuli [31]. The results showed that Tc was not significantly affected by different ISI, whereas Dm was significantly greater using an ISI of 10 s than 30 s [31]. Notably, Tc decreased significantly during ten consecutive stimuli, irrespective of the ISI, whereas Dm was not affected [31]. These findings are relevant for assessing the muscle contraction velocity using Vc. An increase in Vc can be expected, if Dm increases while Tc remains unchanged as a higher displacement amplitude is achieved within the same time. Similarly, an increase in Vc can be also expected, if Tc shortens while Dm remains unchanged, as the same displacement amplitude is achieved within a shorter time. According to Wilson et al. [31], these changes in Dm and Tc during repeated stimulation may be explained by a potentiation effect. Indeed, repeated low-frequency electrical stimulation can induce post-tetanic potentiation [56], which leads to increased peak force, decreased time to peak force and increased rate of force development during an electrically evoked twitch [57]. Thus, it is conceivable that such a potentiation effect could also lead to an increase in Vc.

In contrast, Latella et al. [32] found no significant effect of ISI (10 s, 20 s) on Dm or Tc of the biceps brachii muscle, measured across three different joint angles and two days. Consequently, they concluded that an ISI of 10 s is sufficient during five consecutive stimuli to avoid the effects of fatigue or potentiation. However, both studies did not report Vc, so the effect of ISI during repeated stimulation on Vc is still unclear. Therefore, our results will contribute relevant information on methodical considerations for the determination of Vc using TMG.

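### The inter-stimulus-interval (ISI) ANOVA omits block position and drops a participant for one missing curve, so the second aim may lose precision needlessly, though without expected bias

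*Protocol article*

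**What the plan says.** - Order (Experimental approach): "We will randomize the order of the three blocks with the different ISI for each participant". Randomization and blinding specifies "a block randomization procedure with four blocks of six unique numbers". Four blocks of six make 24, the planned sample, and three intervals have 3! = 6 orders. Four participants per order is the natural reading, though the article does not spell it out.
- Timing (Experimental approach): "The rest period between block 1, block 2 and block 3 will be three minutes". The first block starts three minutes after the day-two progressive stimulation.
- Data used (Experimental set-up and procedures): "From block 1, block 2 and block 3, we will use every single displacement curve for further analysis". That is 3 × 10 = 30 curves per muscle, without averaging.
- Model (Statistical analysis): "we will employ a within-subject repeated-measures ANOVA", and "The two independent variables will be ISI (10 s, 20 s, 30 s) and stimulus number (stimulus 1 to stimulus 10". The factor list is closed, and neither position nor sequence is in it.
- Missing data (Statistical analysis): "Missing data will be handled by listwise deletion of cases with missing data".
- Physiology (Discussion): "repeated low-frequency electrical stimulation can induce post-tetanic potentiation". The same section reports that contraction time fell over ten stimuli whatever the interval, and calls a resulting rise in the rate of displacement conceivable.

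**The concern.** The design takes the trouble to balance position, but the analysis does not use it. If the muscle changes between the first and third block, each participant's three block means differ for a reason other than ISI. Balance keeps that difference out of the ISI means, but a model without position counts it as noise.

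The second fault is independent of drift. A classical repeated-measures ANOVA needs every cell, so under listwise deletion one unusable curve discards the other 29 for that muscle.

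Both faults push the ISI test towards non-significance. That matters because the study is meant to inform a standard rest interval, and the Discussion cites a study that moved from a non-significant interval effect to the conclusion that 10 s is sufficient. An insensitive test would favour the same conclusion here. Both the factor list and the missing-data rule are stated in the article, so these are choices it fixes and not details left to a later document.

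**Working it through.** **The plan's own sample sizes.** Noncentral F, between effect, df 2 and N − 3, λ = f² × N × nonsphericity coefficient, alpha 0.01, power 0.95 (a reconstruction of the cited function):
- f = 3.1, coefficient 0.7: N = 9 (stated 9).
- f = 1.6, coefficient 0.6: N = 19 (stated 18; power at 18 is 0.940).
- ICC 0.92, two measurements, interval width 0.15: 8 × 1.96² × 0.08² × 1.92² / (2 × 0.15²) + 1 = 17.1, so 18 (stated 18).

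The stated sizes reproduce closely, and 18 is the largest stated requirement.

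**Effect of omitting position.** Let s be the within-participant SD of a block mean and d the change per block position, so total drift is 2d. Both d and the ISI effect are assumptions.
- Position deviations for a participant are −d, 0, +d, with sum of squares 2d². Over 24 participants this is 48d².
- With four participants per order, none of it reaches the ISI means. All of it goes into the error, which has 2 × 23 = 46 df.
- Error multiplier = 1 + (48/46)(d/s)² = 1 + 1.043(d/s)².
- Total drift 0.5, 1 or 2 SD (d = 0.25, 0.5, 1 s): × 1.07, × 1.26, × 2.04.

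Take an ISI effect of 0.8/0.4/0 SD. The deviations from the mean are 0.4, 0, −0.4, so λ = 24 × 0.32 = 7.68. Without drift, the noncentral F gives 66.8% power on (2, 46) df and 66.7% on (2, 44) df. The position term therefore costs almost nothing. Simulation with drift:

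| Total drift (SD) | Power, position omitted | Power, position included | Type I error, position omitted |
|---|---|---|---|
| 0 | 67% | 67% | 5% |
| 0.5 | 64% | 67% | about 4% |
| 1 | 56% | 67% | about 2–3% |
| 2 | 26% | 67% | about 0.2–0.4% |

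With position included, type I error stays at about 5%.

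**Listwise deletion.** With independent losses at rate q per curve (assumed; the article gives no rate), P(participant lost from one muscle's ANOVA) = 1 − (1 − q)³⁰:
- q = 0.2%: 6% lost, 22.6 of 24 left on average.
- q = 0.5%: 14% lost, 20.6 left.
- q = 1%: 26% lost, 17.8 left, with a 44% chance of fewer than 18.

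The article does not say whether a loss in one muscle also removes the other. If it does (60 curves), the averages left at 0.5% and 1% are 17.8 and 13.1.

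**Effect of deletion on balance.** The shift in the 10 s versus 30 s contrast, in units of d, has mean absolute size 0.06 after one random deletion (maximum 0.09), 0.10 after four (maximum 0.40) and 0.14 after six (maximum 0.56). With d = 0.5 s and four deletions, 0.10 × 0.5 = 0.05 SD, against a contrast standard error of √(2/20) = 0.32 SD. With no ISI effect, position omitted and two to six random deletions, simulated type I error stayed below 5% (about 3% at 1 SD total drift, below 1% at 2 SD).

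**The case against.** **Randomised, balanced order with a repeated-measures ANOVA is already valid.** This stands. A reader might infer that deletions let drift leak into the ISI estimate and bias it. The documents do not support that. Deletion unrelated to order adds no expected bias, the typical shift is a small fraction of the standard error, and nothing in the article suggests that losses cluster in one order.

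**Drift across blocks is not documented.** This also stands. A reader might infer that the authors expect it, but the Discussion only calls potentiation conceivable. The fall in contraction time that it reports is within ten stimuli, not across blocks. Three minutes of rest may remove it, and the Discussion also cites a biceps brachii study that found 10 s enough to avoid fatigue or potentiation over five stimuli. The loss therefore ranges from nil upward.

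**The 67% baseline is not the plan's scenario.** Correct. With the planned f = 1.6, coefficient 0.6, N = 24, the between-effect formula and alpha 0.05, power is 99.9% without drift, 99.7% with the error × 1.26 and 95% with it doubled. For f = 3.1 it stays at 100%. Those effect sizes are a weak safeguard, however. The normalised rate is 0.8/Tc and depends on contraction time alone, which the Introduction says was not significantly affected by ISI in the study that supplied the planning data.

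**The curve-loss rates are assumed, and 24 allows for dropout.** Also correct: at 0.5% the average of 20.6 still exceeds 18. The margin goes only near 1%, or sooner if both muscles are tied together.

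**A careless mixed model could do harm.** This stands and shapes the fix. With random intercepts alone and no true stimulus effect, simulated type I error for stimulus number was 8–11% under AR(1) correlation of 0.5–0.8. It was 14–28% when participants differed in their stimulus trend (slope SD 0.5–1). A Greenhouse–Geisser-corrected ANOVA gave about 4–6%.

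**Conclusion.** The point holds as one of avoidable imprecision in the second aim. Leaving position out makes the ISI test conservative to a degree that depends on drift the documents do not quantify: no loss without drift, about 11 percentage points of power at 1 SD total drift and about 41 at 2 SD. These figures assume an ISI effect of 0.8/0.4/0 SD and a linear drift; neither is a protocol figure. The balance argument also assumes four participants per order. Listwise deletion adds a loss of 6% to 26% of participants per muscle at assumed curve-loss rates of 0.2% to 1%. The documents do not support a claim of a biased ISI estimate or an inflated type I error. Because the position term costs almost nothing when drift is absent, the change is worth making before preregistration.

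**What to change.** For each rate formula and muscle, add block position (1–3) as a fixed effect to the ISI analysis. Fit a linear mixed model on all available curves with ISI, stimulus number, their interaction and position, in place of listwise deletion for this analysis. Random intercepts alone are not enough: they assume equal correlation across ten successive stimuli, whereas the sample size section itself plans for nonsphericity of 0.6 to 0.7. Specify a covariance that allows serial correlation and individual trends, for example AR(1) errors within block plus a random participant slope for stimulus number, with small-sample degrees of freedom.

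A simpler alternative is to keep the repeated-measures ANOVA for stimulus number, with a sphericity correction named in the text, and to test ISI on participant-by-block means with position in the model.

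The cost is two degrees of freedom, a missing-at-random assumption and slightly more complex code. Block order is already fixed by the randomisation, so no new data, visits or participants are needed.
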